## Abstract

**Background:**

It is estimated that up to 50 % of motor vehicle crash survivors develop significant psychological distress, such as depressive mood and anxiety, within 6 months of the crash. Associated impacts include loss of employment, delayed return to work, financial and familial stress, and increased medical and compensation costs. The major aim of this research is to investigate the efficacy of interventions for preventing the development of psychological distress following a motor vehicle crash. The efficacy of two brief interventions will be examined: a cognitive behaviour therapy (CBT) programme, targeting mood and anxiety, and a lifestyle programme, targeting sleep, diet and physical activity.

**Methods/design:**

This is a randomized, controlled multisite study. Participants include at least 180 adults injured in a motor vehicle crash who have entered a compensation process. Research will compare outcomes in three groups randomly assigned to: one group of 60 adults, who receive a brief email-delivered CBT programme, with one session every 2 weeks for 10 weeks and telephone contact every 2 weeks; a second group of 60 adults, who receive a brief email-delivered lifestyle intervention involving one session every 2 weeks for 10 weeks with telephone contact; and an active waiting-list control group of 60 adults who are provided claims processing-related reading material along with telephone contact every 2 weeks for 10 weeks. Participants will be recruited within 12 weeks of the motor vehicle crash, and will be comprehensively assessed before and after treatment, and 6 and 12 months post-injury. Assuming an *α* probability level of 0.05 and a power of 80 %, at least 180 participants will be recruited. The primary outcome measure is the presence and severity of psychological distress or disorder. Secondary outcome measures include assessment of self-efficacy, resilience employment status, social activity and support, lifestyle and physical health factors, along with process outcome measures of treatment acceptability, feasibility and generalizability.

**Discussion:**

This study will determine whether brief email-delivered interventions distributed soon after the injury and entry into the claims process can be effective in preventing the development of psychological distress.

**Trial registration:**

ANZCTR, ACTRN12615000326594. Registered on 9 April 2015.

**Electronic supplementary material:**

The online version of this article (doi:10.1186/s13063-016-1455-5) contains supplementary material, which is available to authorized users.

## Background

Psychological distress is a common problem for those who have sustained a motor vehicle crash. For those who have entered the compensation system, the level of distress appears to be even more elevated [1]. Pain, injury, impairment, loss of income, trauma, depression and anxiety are common outcomes for survivors of motor vehicle crashes, and in an environment where coping capacity is already challenged, motor vehicle crash survivors are at risk of developing severe psychological disorders, such as major depressive disorder and post-traumatic stress disorder [1]. Such an outcome for motor vehicle crash survivors entering compensation systems is understandable, given the multiple post-injury stressors that can have an impact. Examples of possible stressors include continual reminders of crash-related trauma, when providing oral or written detailed accounts of the accident to insurance organizations, medical experts and legal representatives, reduced social participation and relationship conflicts [1]. It is estimated that up to 50 % of motor vehicle crash survivors will develop elevated psychological distress within 6 months of a crash [1], suggesting that addressing the risks associated with psychological distress early in the compensation process will be of benefit to at-risk people, as well as their employment capacities, families, employers and insurance companies [2].

Interventions that have potential for preventing the development of psychological distress and thus facilitate recovery following a motor vehicle crash are worthy of investigation. For example, motor vehicle crash survivors who file compensation claims could be educated in distress management early in the compensatory process, with the goal of enhancing psychological, social and behavioural skills. Alternatively, lifestyle programmes that improve sleep, diet and exercise might also better position survivors, improving their resilience and coping skills [3–5].

Cognitive behaviour therapy (CBT) is acknowledged as an efficacious treatment [1, 6], further evidenced by its support from government-sponsored initiatives [1]. Strategies used in CBT are pragmatic and effective, with easy-to-learn skills, such as problem solving, anxiety and mood management, in addition to psycho-education about stress and mental health. The efficacy of CBT has been established for mental health disorders, including depression, post-traumatic stress disorder and anxiety, and its efficacy has been demonstrated across a variety of clinical research studies [1, 5, 7–9]. Therefore, CBT should benefit those who have experienced a motor vehicle crash, and who are engaged in the compensation system.

Additionally healthy lifestyle programmes have also been demonstrated to have positive health outcomes in various populations and communities [4, 5, 10]. While there are a limited number of studies that have investigated the efficacy of healthy lifestyle strategies for mental health, current research suggests that positive mental health is independently associated with lifestyle features, such as regular physical activity [3]. Conversely, reduced physical activity has been found to be associated with health risks, such as coronary heart disease, Type II diabetes, some cancers, obesity, hypertension, depression and anxiety disorder [11]. Physical fitness, indicated by a lower heart rate, was found to be associated with smaller inflammatory responses to mental stress as well as great parasympathetic control (e.g. through increased vagus nerve activity or lower neural arousal reactivity to stress) [3]. These factors are known protective factors of mental health disorders, such as depression [12]. Similarly, poor sleep quality has been associated with a variety of health behaviours, impairment and quality of life [13]. A systematic review of healthy lifestyle programmes delivered by internet [4] revealed that such factors as peer and professional support, regular email or phone contact and education were related to increased adherence and better outcomes in participants.

The internet has provided a new format for delivering CBT or healthy lifestyle interventions, by way of an online bibliotherapy with therapist contact [14]. Here, the client is exposed to the same components as with traditional face-to-face treatment; however, the psycho-educational material and instructions for behavioural change are delivered using an internet-based treatment platform [9]. A recent systematic review identified that an online-delivered CBT programme was cost-effective compared with face-to-face CBT, based on improvements in symptoms and reduction of time and resource demands on clinicians [9]. However, recent research has suggested that online-delivered CBT designed to treat depression is no more effective than usual face-to-face care [15]. Here, the low user engagement might have reflected the fact that direction to a website is perceived as impersonal and requires a degree of motivation perhaps unavailable to a clinically depressed person [15, 16]. For this trial, the intervention will be delivered by email and is expected to have similar efficacy to an online programme [9], with the advantage of substantially reduced web-based developmental costs, as well as a more personally delivered CBT treatment via email in addition to telephone support specific to CBT strategies of gentle guidance and support of specific skills and strategies.

To our knowledge, there have only been six randomized controlled trials investigating the prevention of psychological distress following a motor vehicle crash. All six have involved relatively small samples [17–22]. Of these, only two specifically focused on compensatory claimants [17, 18], and these both had non-significant results. However, other studies have reported significant results in reducing symptoms of psychological distress in people with elevated distress levels following a motor vehicle crash using CBT. For example, CBT techniques involving exploration of thoughts and feelings and *in-vivo* exposure [23, 24] and cognitive restructuring [25] have either contained or reduced symptoms of anxiety, depression and post-traumatic stress disorder for motor vehicle crash survivors. These promising results suggest that a randomized controlled trial involving interventions such as CBT, and designed to prevent development of psychological distress, employing a sample size with sufficient power to detect a true finding, is warranted. The uniqueness of this trial is that it will investigate the efficacy of interventions designed to prevent development of psychological distress for people entering the compensation system following a motor vehicle crash. Participants will be included, regardless of whether or not they have symptoms of psychological morbidity.

### Aims of the study

The major aim of the study is to evaluate the effectiveness of an intervention designed to prevent development of psychological distress following a motor vehicle crash and delivered within 12 weeks of the crash. A secondary aim is to achieve a relatively high rate of adherence and participant satisfaction with email-delivered programmes, consistent with other studies of online-delivered CBT treatments [26]. Primarily, the treatment interventions aim to prevent the development of psychological distress, along with producing clinically and statistically significant improvements in health outcomes, such as reduced anxiety and depressive mood, increased physical activity, improved sleep, improved quality of life and disability ratings, reduced pain severity, and improved return to pre-injury employment and daily functioning in the medium term after the programme. Table 1 shows the flow of the trial’s recruitment, intervention and assessments.

**Table 1 Tab1:** SPIRIT flow chart for recruitment, treatment and assessments

	Study period							
	Enrolment	Randomization	Treatment (5 fortnightly emailed programmes with phone calls)					6 and 12 month follow-up sessions
Time point	−*t* _1_	0	T1	T2	T3	T4	T5	
Recruitment:								
Eligibility screen	×							
Informed consent	×							
Randomization		×						
Interventions:								
Cognitive behaviour therapy			×	×	×	×	×	
Lifestyle			×	×	×	×	×	
Waiting-list control			×	×	×	×	×	
Assessments:								
1. Baseline (demographics, lifestyle, health)		×						
2. Post-treatment lifestyle, health, process outcomes							×	
3. 6-month lifestyle, health								×
4. 12-month lifestyle, health								×

## Methods/design

This study is designed as a three-arm randomized controlled trial with two active interventions and one active waiting-list control. The first is a brief email-delivered CBT treatment, consisting of five modules delivered fortnightly. The second is a brief email-delivered lifestyle treatment, also consisting of five modules and delivered fortnightly. Both groups will also receive weekly telephone contact to encourage their engagement with their programmes. The active waiting-list control group will receive reading material about the claims process, and will also receive fortnightly follow-up phone calls; however, these calls will only involve brief discussions of their progress in the compensation scheme in addition to confirming that they are receiving their reading material. There will be four measurement points: baseline (within 12 weeks of the motor vehicle crash), post-treatment (within 2 weeks of cessation of the interventions), and 6-month and 12 month follow-up sessions for the treatment groups (from the time of entry into the study) with the final two assessments also including participant satisfaction and acceptability questionnaires. If participants in the waiting-list control group do not want to receive either of the intervention programmes, they will also be assessed at 12 months.

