### Sample size

Based on prior results of CBT and healthy lifestyle interventions [1, 4, 5], the two interventions are assumed to have at least a small to moderate mean effect size of 0.25 (Cohen’s *d*) when compared with the control group. Assuming an α probability of 0.05 and a power of 80 % for a three-group comparison analysis with four measures over time, a sample of 135 participants must be recruited to detect a true difference (see Fig. 1). It is therefore proposed to recruit at least 180 adult participants, randomly assigned to one of the three groups each with at least 60 participants per group. This is to accommodate for the loss to follow-up of approximately 25 % of participants, based on similar research [27].

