### Interventions

All participants will be randomly assigned to one of three groups: (i) CBT, (ii) lifestyle or (iii) waiting-list control. For the two treatment groups, participants are delivered fortnightly modules presented in Microsoft PowerPoint presentation with homework worksheets and templates for self-monitoring and practising learnt skills. Emails are brief with two or three paragraphs containing three or four concise sentences as well as a brief case study followed by a weekly summary. At the beginning of every other week, participants are telephoned for a maximum 10 min conversation aimed at (i) encouraging the learning and practising of skills from the previous week, (ii) ‘normalizing’ the challenges of learning new skills, (iii) emphasizing that symptom reduction requires gentle but consistent practice of the skills over time, and (iv) reminding participants about unread materials. The control group is also emailed fortnightly; however, this is restricted to reading information relating to the claims process, and phone calls are aimed at ensuring they are receiving and reading this information. The control group will be offered the programme of their choice, or the programme analyzed as more efficacious after their 6-month follow-up assessment. The contents of each module for each group (original version, March 2015) are presented in Table 2.

**Table 2 Tab2:** Contents of modules for cognitive behaviour therapy, lifestyle and waiting-list control groups

	Cognitive behaviour therapy	Lifestyle	Control
1	Overview	Overview	Reading: ‘A guide for people injured in a motor vehicle crash’
2	Mood and slow breathing skills, self-monitoring	Goal setting and life pacing	Reading: ‘Overview of the claims process’
3	The art of distraction, applying distraction	Self-monitoring and changing unhelpful behaviours	Reading: ‘Obligations of the insurer’
4	Stress and helpful thinking, evidenced-based thinking	Sleep hygiene and sleep self-monitoring	Reading: ‘Obligations of the claimant’
5	Problem solving and conclusions, self-mastery, changeable versus unchangeable problems	Improving well-being through diet and physical exercise, social participation, daily activity schedule	Reading: ‘Finalizing a claim’

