### Outcome measures

#### Primary and secondary measures

Table 3 shows the primary and secondary outcome measures. The primary outcome measure is the presence and severity of psychological distress or disorder across four time points assessed by a mixture of psychometric mental health measures and diagnostic interviews based on criteria of the fifth edition of the *Diagnostic and Statistical Manual of Mental Disorders* for depression, anxiety and post-traumatic stress disorder. Secondary outcome measures will include motor vehicle crash injury history, employment, social life, resilience and self-efficacy, as well as indicators of physical health and lifestyle.

**Table 3 Tab3:** Primary and secondary outcome measures acrossbaseline, post-treatment and follow-up

Measure	Primary	Secondary	Baseline	3 months	6 and 12 months
Demographics					
Sex, age, weight, height		×	×		
Marital status		×	×		
Highest level of education		×	×		
Motor vehicle crash history					
Motor vehicle crash date		×	×		
Driver or passenger		×	×		
Perception of danger during motor vehicle crash		×	×		
Hospital admission: yes or no		×	×		
Days spent in hospital		×	×		
Involvement of lawyer		×		×	
Referral to psychologist or psychiatrist		×		×	
Satisfaction with claims process: 3-point Likert scale		×			×
Claim finalization: yes or no		×			×
Employment					
Pre-motor vehicle crash employment: part-time, full-time, pensioner		×	×		
Modified hours since motor vehicle crash: yes or no		×	×	×	×
Returned to work: yes or no		×	×	×	×
Expectation of return to work: 11-point Likert scale		×	×	×	×
Reason for non-return to work		×	×	×	×
Number of days after motor vehicle crash for return to work		×	×	×	×
Social life					
Returned to activities after motor vehicle crash: yes or no		×	×	×	×
Expectation of return to pre-motor vehicle crash activities: 11-point Likert scale		×	×	×	×
Pre-motor vehicle crash social activity quality		×	×	×	×
Satisfaction of pre-motor vehicle crash social supports: 11-point Likert scale		×	×	×	×
Satisfaction of pre-motor vehicle crash social engagements		×	×	×	×
Expectation of return to pre-motor vehicle crash activities: 11-point Likert scale		×	×	×	×
Pre-motor vehicle crash relationship quality: 5-point Likert scale		×	×	×	×
Lifestyle habits					
Alcohol: Alcohol Use Disorders Identification Test	×		×	×	×
Smoker: yes, no, amount per day		×	×	×	×
Health					
Health Status: SF-12		×	×	×	×
Psychology or psychiatric history: yes or no		×	×	×	×

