### Hypothesis and data analysis

The primary hypotheses assert that brief interventions (CBT and healthy lifestyle) will prevent the development of psychological distress by improving psychological coping skills and healthy behaviours. A further hypothesis is that the intervention groups will show improved resilience and quality of life compared with the control group; however, we are not hypothesizing a significant difference between the treatment groups themselves.

The effectiveness of the interventions will be determined by conducting multivariate analyses of variance with repeated measures for revealing differences within and between groups, as well as reporting effect size changes. Potential confounding factors, such as pre-injury health and education, will be adjusted for in the analysis. Correlation analyses and multiple regression will also be used to analyse predictors of psychological distress over time. The intervention satisfaction questionnaire will be analyzed to assess participant satisfaction of the overall treatment approach. Clinically significant improvements or recovery will be determined by identifying the proportion of participants who demonstrate a significant reduction in their symptoms.

An interim analysis will re-evaluate the assumptions made for the study’s sample size calculation, with re-estimation made if required, unless the trial needs to be stopped as a result of significant and consistent indications of elevated psychological distress associated with the interventions, according to the safety measures and endpoint.

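### The primary three-group comparison runs over four time points, but at 12 months the plan has no intact, untreated randomised control group

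*Protocol article*

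**What the plan says.** All references are to the protocol article.

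- **Methods/design (opening paragraph)** lists four measurement points. The later two are described as "6-month and 12 month follow-up sessions for the treatment groups (from the time of entry into the study"). The paragraph then adds that, if members of the waiting-list "control group do not want to receive either of the intervention programmes, they will also be assessed at 12 months".
- **Interventions:** "The control group will be offered the programme of their choice, or the programme analyzed as more efficacious after their 6-month follow-up assessment".
- **Primary and secondary measures:** the primary outcome is the "presence and severity of psychological distress or disorder across four time points".
- **Sample size:** the calculation is for a "three-group comparison analysis with four measures over time". It gives 135 participants, raised to 180 for about 25 % loss.
- **Hypothesis and data analysis:** effectiveness is to be judged by "multivariate analyses of variance with repeated measures for revealing differences within and between groups", with adjustment for potential confounders.
- **Abstract, Table 1 and Table 3:** each shows a 12-month assessment with no restriction on the control arm.

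None of these places names a last occasion for the control contrast, or says how a partial control arm at 12 months is to be handled.

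**The concern.** On the plain reading of Methods/design, who is assessed in the control arm at 12 months depends on a choice made after randomisation. The programmes target mood, anxiety, sleep and activity, so that choice may well be related to distress, which is the primary outcome. Those who decline are then not a fair stand-in for the randomised control arm.

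If the abstract and tables are followed instead and every control is assessed, the groups remain as randomised. But controls who accepted have been offered an intervention by then, so the contrast is no longer treatment against no treatment.

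Either way, the primary outcome and the power statement include an occasion at which the intended comparison does not exist. What is at stake is any claim that the interventions prevent distress out to 12 months, and possibly the earlier contrasts if all four occasions are analysed together on complete cases.

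**Working it through.** **1. The plan's own figure.**
- The inflation step reproduces: 135 / (1 − 0.25) = 180, or 60 per arm; 60 × 0.75 = 45 per arm evaluable.
- The 135 depends on a within-person correlation ρ that the text does not state (the power figure is not shown). For the between-groups test in a repeated-measures ANOVA with m occasions, the noncentrality is λ = N·m·f² / (1 + (m − 1)ρ).
- With f = 0.25, m = 4 and ρ = 0.8, λ = 135 × 4 × 0.0625 / 3.4 = 9.93 and power is 80.3 %, so 135 comes out. At ρ = 0.5 the same test needs 102, and at ρ = 0.9 it needs 147. So f = 0.25 with ρ = 0.8 is an assumption that fits, not a stated input.

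**2. Which contrasts are affected.**

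| Contrast | Post-treatment | 6 months | 12 months |
|---|---|---|---|
| CBT or lifestyle vs control | randomised | randomised (programme offered afterwards) | decliners only, or crossed over |
| CBT vs lifestyle | randomised | randomised | randomised |

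**3. Controls left if all four occasions are analysed on complete cases.** Uptake is not given, so it is assumed. Controls kept = 45 × (1 − uptake): 45 × 0.5 = 22.5, about 22, at 50 % uptake; 45 × 0.3 = 13.5, about 14, at 70 %. With f = 0.25 and ρ = 0.8, power is 80 % if all controls decline, 71 % if 75 % decline, 57 % if 50 % decline and 34 % if 25 % decline.

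**4. Size of the selection effect at 12 months.** Assumptions: no other loss; probability of accepting = 1 / (1 + exp(−s·z)), where z is standardised 6-month distress (50 % uptake overall); all correlations between occasions 0.6.
- Raw shift at 12 months = 0.6 × mean z among decliners.
- Decliners are shifted by the same amount at baseline, because that correlation is also 0.6. Baseline-adjusted shift = raw shift − 0.6 × baseline shift. For s = 1: −0.25 − 0.6 × (−0.25) = −0.10.

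| Slope s | Decliners at 6 months (SD) | Raw shift at 12 months (SD) | After baseline adjustment (SD) | Modelling baseline and 6 months (SD) |
|---|---|---|---|---|
| 0.5 | −0.24 | −0.14 | −0.06 | 0.00 |
| 1 | −0.41 | −0.25 | −0.10 | 0.00 |
| 2 | −0.61 | −0.36 | −0.15 | 0.00 |

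The negative sign means that controls look less distressed than they should, which works against the interventions. It reverses if the more distressed decline. The last column is zero because, in this model, uptake depends only on a score that was measured.

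**5. Cost of dropping to three occasions.** With m = 3, λ = 135 × 3 × 0.0625 / 2.6 = 9.74 and power at 135 is 79.5 %, against 80.3 % with four. The N for 80 % becomes 138, or 138 / 0.75 = 184 recruited.

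**The case against.** **Methods/design never says that accepters are not assessed at 12 months.** It says that decliners will also be assessed. The phrase about the treatment groups covers the 6-month session too, yet Interventions gives controls a 6-month assessment, so the phrase cannot be a strict exclusion. This stands in part: the restriction is the natural reading, but the abstract and tables contradict it. It does not rescue the contrast, because assessing everyone replaces self-selection with cross-over.

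**A reader might infer that the primary analysis compares treated arms with self-selected decliners at every time point.** The document does not support that. It names a repeated-measures MANOVA but states no complete-case rule, and missing-data handling may be set out in a plan not shown. The inference holds only if the four-occasion analysis is run on complete cases.

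**A reader might infer that no adjustment can remove the bias.** Under the model used here that is wrong: baseline adjustment cuts it to 0.06 to 0.15 SD, and modelling 6-month distress removes it. What remains is that uptake may depend on things not measured, and no calculation bounds that.

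**A reader might infer that the bias equals the whole planned effect.** The raw shift at slope 1 is 0.25 SD, and the Sample size section labels its 0.25 as Cohen's d. But the between-groups calculation that gives 135 uses 0.25 as f. With two equal treated arms against control, that corresponds to d = 0.25 × 3 / √2 = 0.53, so the raw shift would be about half of it.

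**Offering the programme to controls after 6 months is ordinary in a waiting-list trial.** Agreed, and the offer is not criticised here. The problem is keeping the 12-month occasion inside the primary three-group comparison.

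**Conclusion.** The concern holds in a limited form. The primary outcome and the sample size include a 12-month occasion at which no intact, untreated randomised control group is planned. Depending on which text governs, the intervention-versus-control contrast at that occasion is selected after randomisation or contaminated by cross-over. This contradiction rests on the document alone.

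The earlier control contrasts, and CBT versus lifestyle at 12 months, are sound unless a complete-case four-occasion analysis discards accepters' earlier data.

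The size of the bias rests on assumed uptake, slope and correlation, none of which the document gives. The figures in the working show what is plausible and are not an estimate for this trial. Unmeasured reasons for uptake could leave bias of unknown size and sign. The point is worth correcting because it decides what the trial can conclude at 12 months.

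**What to change.** 1. Define the primary three-group comparison on baseline, post-treatment and 6 months. Change four to three for that comparison in Sample size and in Primary and secondary measures.
2. For 12 months, choose one of these:
   - report within-arm durability and CBT versus lifestyle, with no causal contrast against control; or
   - assess all randomised controls at 12 months whatever they chose, analyse them as randomised, and label the contrast immediate versus deferred offer.
3. Reconcile the abstract, Table 1, Methods/design, Sample size, Interventions, and Primary and secondary measures with Table 3, so that they agree on who is assessed at 12 months.

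**Cost.** Steps 1 and 3 need only wording. Power at 135 moves from 80.3 % to 79.5 % on the assumptions above. The first option in step 2 gives up any controlled 12-month claim. The second needs 12-month assessments of the controls who accepted: about 30 of the 60 randomised at an assumed 50 % uptake (60 × 0.5), and at most 60.
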